### Secondary outcome measures

3.8

The secondary outcomes will be the quality of life and the levels of anxiety and depression after the intervention, which will be evaluated by the Euroqol and HADS, consecutively. Additional secondary outcomes include the incapacity level, the degree of neurological deficit severity, the functional capacity for basic daily life activities and spasticity of the lower limb affected after the stroke, which were evaluated using the mRs, NIHSS, BI, and mAS.

### Sample size calculation

3.9

The sample will be composed of 50 volunteers randomized into 2 groups to receive 1 of 2 types of AFO. This number of participants are capable to detecting a 30% difference in improvement of the primary outcome (TUG and TSMB) with an alpha error of 0.05 and beta error of 0.2.

### Baseline assessments

3.10

#### Sociodemographic evaluation

3.10.1

Sociodemographic data will be collected from the participants, as well as data on currently used medications, previous diseases, and previous physiotherapy treatments.

### Neurological and functional evaluation

3.11

The participants will be classified according to the incapacity that the stroke caused by mRs. The scoring on this scale varies from 0 to 6, with 0 indicating lack of incapacity and 6 indicating fatality.^[23]^

The NIHSS is widely utilized, valid, and reliable. It enables quantification of the severity of neurological deficits after stroke and evaluates 11 items: consciousness level, ocular deviation, facial paresis, language, speech, negligence, motor function, limb sensitivity and ataxia. Its scoring varies from 0 (no evidence of neurological deficits for the tested sphere on the scale) to 42 (patient in a coma and unresponsive).^[24]^

The Euroqol is a validated scale that includes 5 questions addressing mobility, personal care, usual activities, pain/discomfort and anxiety/depression. The patients will respond according to their perception of health and then will indicate their perception on a ruler from 0 to 100 with 0 and 100 signifying the worst and best health status, respectively.^[25]^

The HADS scale briefly evaluates the levels of anxiety and depression in individuals with physical pathology and in ambulatory treatment; it is composed of 14 questions, including 7 on depression and 7 on anxiety.^[26]^

The TSMB assesses the performance of balance and the presence of alterations in the gait. It is composed of 16 items observed by the evaluator, including 9 for body balance and 7 for gait. It classifies aspects of gait, such as velocity, stepping distance, symmetry, 360° gyrations, balance, and changes with the subject's eyes closed. The score on each item varies from 0 to 1 or from 0 to 2 in which the lower the score, the poorer is the physical ability. The maximum score is 16 points for balance and 12 for gait with a total of 28 points. Scores below 19 points represent a high risk of falling, while those between 19 and 24 points represent a moderate risk of falls.^[27]^

The TUG test is utilized for evaluation of functional mobility involving velocity, potency, and dynamic balance. It is carried out in the following manner: patients will be seated in a chair, and then, utilizing a stopwatch, a measurement will be made of the time they require to stand up, walk a distance of 3 m, turn around, return, and sit again. The individual will be allowed to use auxiliary gait devices if necessary. The shorter the time to execute the test, the better is the functional performance.^[28]^

The BI measures the degree of assistance the individual requires in 10 activities: feeding oneself, bathing oneself, personal care, dressing oneself, controlling their urinary sphincter, controlling their intestinal sphincter, using the bathroom, executing bed-chair transferals, walking, and climbing a flight of stairs. The scoring varies from 0 to 100, and higher scores indicate a greater degree of functional independence.^[29]^

Spasticity of the affected lower limb will be evaluated by mAS, which is a scale that grades spasticity according to the movement of a muscle group and its resistance to joint movement; its scoring varies from 0 to 4, and the higher the score, the higher is the spasticity severity.^[30]^

### Confounding variables

3.12

This analysis will be adjusted for potential confounders, such as age, sex, mRs at discharge, NIHSS scores, and type of stroke.

### Statistical analysis

3.13

The analyses will follow the principle of Intention to Treat. The Kolmogorov-Smirnov test will be employed to verify the normality of the distribution. The non-categorical data of a parametric distribution will be analyzed by two-way ANOVA for repeated measures, and multiple comparisons will be analyzed with the Tukey test. The categorical data at the baseline moment will be compared using the Chi-Squared test. The nonparametric distribution variables will be categorized as improvement or worsening and compared between groups with the Chi-Squared test. The non-categorical data will be expressed as means and standard deviations, and the categorical data will be expressed as percentages. Statistical significance will be established as *P* < .05.

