### Procedures (Template)

3.4

Post-stroke patients will be evaluated by a physiotherapist and a physician with experience in the evaluation and prescription of AFOs. After evaluation by the team, the patients who have an indication for the use of AFO orthosis and fit the eligibility criteria of the study will be referred for specific evaluation. All the participants will sign terms of free and informed consent for participation in the study.

The individuals who fit the criteria for inclusion in this study will be randomized to receive 1 of the 2 types of orthoses: Fixed AFO or Articulated AFO.

The first evaluation will occur before the patient begins the use of AFO orthosis, and then the patient will be reevaluated 30 days after the intervention (AFO use).

All the scales, questionnaires, and tests that will be applied were already translated, adapted and validated for the Portuguese language used in Brazil. Individuals will be assessed using the Time Up Go Test (TUG), Tinetti's Scale of Mobility and Balance (TSMB), European (5D) Quality of Life Scale (Euroqol), Hospital Anxiety and Depression Scale (HADS), modified Rankin scale (mRs), National Institute of Health Stroke Scale (NIHSS), Barthel Index (BI), and the Modified Scale of Ashworth (mAS).

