### Primary outcome measures

3.7

The primary outcomes will be balance and mobility, which will be evaluated by the TUG and by TSMB. These outcomes will be assessed after the intervention.

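### For a normally distributed primary outcome, the repeated-measures ANOVA with Tukey treats the pre-orthosis value as an outcome; a baseline-adjusted day-30 comparison should be the single deciding test

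*Protocol article*

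**What the plan says.** Section 3.4 fixes two visits (the quote stops just short of the sentence's reference to orthosis use): "The first evaluation will occur before the patient begins the use of AFO orthosis, and then the patient will be reevaluated 30 days after the". Section 3.5 fixes two arms of 25, allocated 1:1.

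Section 3.13 chooses the analysis by a normality check: "The Kolmogorov-Smirnov test will be employed to verify the normality of the distribution". Data that pass "will be analyzed by two-way ANOVA for repeated measures, and multiple comparisons will be analyzed with the Tukey test". Data that fail take another route: "The nonparametric distribution variables will be categorized as improvement or worsening and compared between groups with the Chi-Squared test". One threshold covers everything: "Statistical significance will be established as *P* < .05".

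Two other sections bear on which comparison is meant. Section 3.9 sizes the trial for "detecting a 30% difference in improvement of the primary outcome (TUG and TSMB"), which is a comparison of change. Section 3.7 says of the two primary outcomes: "These outcomes will be assessed after the intervention". Section 3.12 lists adjustment variables (age, sex, discharge mRS, NIHSS and stroke type, given as examples). The baseline TUG or TSMB value is not among them.

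**The concern.** Take one outcome, say TUG. The ANOVA gives tests for group, time and group-by-time, and Tukey adds pairwise comparisons among the four group-by-visit cells. Three of these results compare the two orthoses: the group main effect, the group-by-time interaction and the Tukey pair at day 30.

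The baseline visit precedes any orthosis use, so randomisation makes its expected between-arm difference zero. A model that treats it as a second outcome uses it poorly. The group main effect averages a visit with no treatment effect into the visit that has one. The Tukey day-30 pair pays a penalty for cell comparisons that do not bear on the treatment question, and it ignores the patient's own baseline. The interaction uses baseline by simple subtraction, which is inefficient when the correlation is modest.

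The trial is meant to guide which orthosis is prescribed. With 25 per arm, a real difference could be missed, or the answer could depend on which line of the output is read. This arises within each outcome, so a correction across TUG and TSMB would not remove it.

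**Working it through.** **The plan's own figure.** Section 3.9 gives 50 patients, alpha 0.05 and beta 0.2, but no SD or reference rate, so 50 can be neither confirmed nor refuted. What 25 per arm can detect at 80% power, two-sided, follows from the normal formula: (1.96 + 0.842) × √(2/25) = 0.79 SD. With the t distribution it is 0.81 SD, which is used below.

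**Inputs.** From the document: n = 25 per arm, two visits, alpha 0.05. Assumed: two-sided tests, normal data, SD 1 at both visits, day-30 effect δ = 0.81, and a baseline-to-day-30 correlation ρ of 0.3 to 0.9 (the document gives none). The section 3.12 covariates are left out.

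**Effect and standard error of each test.**
- Group main effect (mean of the two visits): effect (0 + δ)/2 = 0.405; SE = √[((1+ρ)/2) × 2/25].
- Group-by-time (change): effect δ = 0.81; SE = √[2(1−ρ) × 2/25].
- Day 30 adjusted for baseline: effect δ = 0.81; SE ≈ √[(1−ρ²) × 2/25].

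At ρ = 0.3 the effect/SE ratios are 0.405/0.228 = 1.78, 0.81/0.335 = 2.42 and 0.81/0.270 = 3.00. At ρ = 0.9 they are 0.405/0.276 = 1.47, 0.81/0.126 = 6.40 and 0.81/0.123 = 6.57. Each is compared with a critical t of about 2.01.

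| ρ | Group main effect | Group-by-time | Day 30 adjusted for baseline |
|---|---|---|---|
| 0.3 | 41% | 66% | 83% |
| 0.5 | 37% | 80% | 89% |
| 0.7 | 33% | 95% | 97% |
| 0.9 | 30% | 100% | 100% |

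The first two power columns come from the noncentral t distribution. The last is simulated, which allows for chance baseline imbalance. Separate simulation runs agree to within about one percentage point.

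**Tukey at day 30.** SE = √(2/25) = 0.283, so the ratio is 0.81/0.283 = 2.86. The 5% studentized-range point for four cells and 96 degrees of freedom is 3.70, equivalent to a t of 3.70/√2 = 2.61. Power is about 59% at every ρ (simulation 59–60%), against 80% for an unadjusted day-30 t-test.

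**False positives with no true effect.** Each of the main effect and the interaction rejects in about 5% of trials. With equal SDs, a patient's mean and change are uncorrelated, so the chance that at least one rejects is close to 1 − 0.95² = 9.75%. Simulation gives 9.3–10.1%. Adding a correctly scaled Tukey comparison moves this by about 0.1 percentage point or less.

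**Disagreement.** With δ = 0.81 and ρ = 0.7, the interaction is significant and the main effect is not in about 64% of trials.

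**Chance baseline imbalance.** An imbalance d between arms shifts the expected main-effect estimate by d(1+ρ)/2, that is 0.65d at ρ = 0.3 and 0.95d at ρ = 0.9. It shifts the change estimate by −(1−ρ)d. Adjustment for baseline removes it.

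**The case against.** The strongest reply is that the article names a model and an alpha, and that picking the deciding term is commonly left to an analysis plan, which may exist but is not shown. That stands: the unnamed term would not be a finding by itself. The point is the method that section 3.13 does fix, for which a better one is available from data already collected.

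Several stronger readings are tempting, but the document does not support them:
- *The plan will judge superiority on the group main effect.* Nothing says so. The improvement wording in section 3.9 and the improvement/worsening route in section 3.13 both lean toward change, which is the interaction.
- *Sections 3.7 and 3.9 contradict each other.* Section 3.7 states when outcomes are measured. A comparison of change also needs a post-intervention assessment.
- *The plan's error rate is nearly double.* It is so only if a significant main effect or interaction may each count, a rule the document neither states nor excludes.
- *Tukey inflates false positives.* Correctly scaled, it adds almost nothing; its cost is power.
- *Every primary outcome is affected.* An outcome that fails the normality check gets one chi-squared test instead.

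It is also fair that the correlation and effect size are assumed and that the section 3.12 covariates are not modelled. The halving of the main effect depends on neither.

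**Conclusion.** The point holds for a primary outcome that passes the normality check. The specified ANOVA treats the pre-orthosis value as an outcome, and as a result its group main effect carries only half of any day-30 effect. For a 0.81 SD difference and an assumed correlation of 0.3–0.9, power is about 30–41% for that main effect, 59% for Tukey at day 30, 66–100% for group-by-time and 83–100% for the baseline-adjusted day-30 difference. Letting either the main effect or the interaction count would give about 9.5% false positives per outcome.

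The advantage of adjustment over the interaction is largest at low correlation (83% against 66% at 0.3) and disappears near 0.9. The figures rest on equal SDs, normal data and two-sided tests. The halving follows from randomisation alone.

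**What to change.** In section 3.13, for TUG and for TSMB when analysed as normally distributed, make the between-arm difference at day 30, adjusted for the baseline value of the same outcome (ANCOVA, alongside the section 3.12 covariates), the single deciding test: two-sided 0.05, reported with a 95% CI. Name only this contrast. Offering the group-by-time term as an alternative would leave two tests that can disagree.

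Drop the Tukey step for these two-group, two-visit outcomes, and label the group and time main effects descriptive. Make the change before the arms are compared.

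The cost is a change of wording. Baseline and day-30 values are already collected, and no patients are added. The downside is that a significant main effect or Tukey pair can no longer support a claim that one orthosis is superior. The route for non-normal outcomes is not altered by this change.

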### Randomization and blinding

3.5

The process of randomization will be performed using Microsoft Excel for Windows by a researcher who was not involved in the recruitment of participants. The participants will be randomized into 2 groups at a proportion of 1:1 with 25 patients allocated into each group. After evaluation, the participants who are eligible for the study will be referred to a physiotherapist responsible for their specific evaluation.

Because of the nature of the interventions, it will be impossible to blind the therapists and patients involved in the study.

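### A Kolmogorov-Smirnov test on the trial data decides whether each outcome, including TUG and TSMB, is analysed as a mean or cut to improved/worsened; the fallback usually loses much power and has no place for unchanged patients

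*Protocol article*

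**What the plan says.** Section 3.13 (Statistical analysis) sets a rule in three steps.

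- Gate: "The Kolmogorov-Smirnov test will be employed to verify the normality of the distribution".
- If the variable is judged parametric: two-way repeated-measures ANOVA, with Tukey comparisons.
- If not: "The nonparametric distribution variables will be categorized as improvement or worsening and compared between groups with the Chi-Squared test".

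No outcome is exempt, so the rule covers the primary outcomes of section 3.7 (TUG and TSMB) and the secondary scales of section 3.8. The secondary scales include coarse ones. For mAS, section 3.11 says "its scoring varies from 0 to 4, and the higher the score, the higher is the spasticity severity"; mRs runs from 0 to 6. The article does not say which version of K-S is used, whether raw scores, changes or residuals are tested, or what change counts as improvement. Section 3.12 promises adjustment for age, sex, mRs at discharge, NIHSS and type of stroke. Section 3.9 claims power for "detecting a 30% difference in improvement of the primary outcome (TUG and TSMB") "with an alpha error of 0.05 and beta error of 0.2".

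**The concern.** There are four difficulties.

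1. A test on the trial's own data decides whether the primary question concerns a difference in mean change or a difference in the proportion improved. TUG and TSMB could end up on different scales.
2. Reducing change to two classes discards its size. If the cut is at zero, a trivial and a large gain count alike. All patients are within a year of stroke, receive an AFO and have physiotherapy, so most may improve in both arms, and little contrast would then remain.
3. A patient whose score does not change belongs to neither class. This is likely over 30 days on mRs and mAS.
4. A plain chi-squared test cannot adjust for the covariates of section 3.12.

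At stake are the interpretability of the primary result and, in a trial of 50, much of its power.

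**Working it through.** **Inputs from the article.** "The sample will be composed of 50 volunteers randomized into 2 groups to receive 1 of 2 types of AFO" (section 3.9); "randomized into 2 groups at a proportion of 1:1 with 25 patients allocated into each group" (section 3.5); alpha 0.05, power 0.80. No SD, correlation or improvement rate is given, so every value below for these is an assumption. Tests are two-sided and dropout is taken as zero.

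**1. The plan's own figure.** The 50 cannot be reproduced uniquely, because the 30% may be a mean or a proportion.

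- Proportions, absolute 30 points: n = [1.96√(2p̄q̄) + 0.842√(p₁q₁ + p₂q₂)]² / 0.30². For 35% v 65%: (1.386 + 0.568)² / 0.09 ≈ 42.4, so 43 per arm. Across all base rates n runs from 22 to 43.
- Means: n = 2(1.96 + 0.842)² / d². If SD is 0.378 of the mean, d = 0.30/0.378 = 0.794 and n = 25.

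So the article does not settle which of its two branches it was powered for.

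**2. What the gate does.** Simulated rejection rates, n = 25 / n = 50 unless a range is given:

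| Assumed data | Uncorrected K-S | Lilliefors |
|---|---|---|
| Lognormal, log-SD 0.4 | 1% / 5% | 30% / 54% |
| Lognormal, log-SD 0.5 | 3% / 11% | 43% / 71% |
| TSMB-like, mean 18 SD 5 or mean 21 SD 6 | 0–0.4% | within 9–85% |
| TSMB-like with ceiling, mean 24 SD 5 | 1% / 10% | within 9–85% |
| Five-level ordinal score | 17% / 83% | 96% / 100% |

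The 9–85% is the range over all the TSMB-like cases. A second set of five-level runs gave 23–88% and 97–100%. The branch thus depends on the software option as much as on the data.

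**3. Power of the fallback, effect 0.6 SD, correlation 0.7.** SD of change = √(2(1 − 0.7)) = 0.775, so d on change = 0.6/0.775 = 0.775.

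- t-test on change, which is the group-by-time test of a two-time-point ANOVA: Φ(0.775√12.5 − 1.96) = Φ(0.78) ≈ 78%; simulated 77–78%.
- Cut at zero, comparator improves 0.3 SD: proportions improved Φ(0.3/0.775) = 65% and Φ(0.9/0.775) = 88%. Formula power 47%; simulated 49%.
- Cut at zero, comparator improves 0.6 SD: 78% v 94%. Formula power 36%; simulated 38%.
- Mann-Whitney on change: simulated 74–75%. ANCOVA: 82–83%.
- With Yates' correction, which the article neither specifies nor excludes, chi-squared falls to 32% and 18%.

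**4. Power of the fallback, effect set to give the t-test 80% (d = 0.81).** Proportion improved in the other arm = Φ(z(p₀) + 0.81).

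| Comparator improved | Other arm | Chi-squared power, 25 per arm | n per arm for 80% |
|---|---|---|---|
| 50% | 79% | 58% | 42 |
| 60% | 86% | 53% | 47 |
| 70% | 91% | 46% | 56 |
| 80% | 95% | 36% | 75 |
| 90% | 98% | 23% | 130 |

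**5. Non-normal change, the case the fallback is meant for.** Simulated, Mann-Whitney v chi-squared, as the comparator's improvement rate rises:

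- left-skewed (50–80%): 94% v 61% falling to 22%;
- heavy-tailed, t with 3 df (50–80%): 75–76% v 66% falling to 28%;
- skewed TUG-like (50–89%): 71% falling to 50% v 60% falling to 20%;
- right-skewed with a sharp lower edge (50–80%): 94–95% v 76–99%. Chi-squared was the more powerful at 50–70% and the less powerful at 80%.

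**6. Unchanged patients.** Assume 10/60/30% worse/unchanged/improved in one arm and 5/35/60% in the other. Chi-squared power is 62% if unchanged counts as not improved, 8% if it counts as not worsened, and 25% if unchanged patients are dropped. Dropping leaves 25 × 0.40 + 25 × 0.65 = 26.25 of 50, which sits badly with the stated intention-to-treat principle. Mann-Whitney on the three categories has 55%, so here one coding of the dichotomy does slightly better. The spread from 8% to 62% is the problem.

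**The case against.** Five things can be said on the other side.

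- **The primary outcomes may seldom reach the fallback.** This stands under uncorrected K-S. A reader might infer that TUG and TSMB will be analysed by chi-squared, or that K-S is nearly blind to skew. Each holds only under a particular version of the test, and the article names none. With the uncorrected version the gate misses skew and the harm falls mainly on short secondary scales; with Lilliefors the gate detects skew and the primary outcomes are exposed.
- **The power figures in steps 3 and 4 use normal data, which the plan would normally send to ANOVA.** This stands; they are illustrations. Step 5 covers non-normal change, and most shapes still lose power. A reader might infer that dichotomising never helps. The right-skewed case and one coding in step 6 contradict that.
- **ANCOVA is not the plan's alternative.** This stands. The fair comparison is 77–78% for the t-test on change; the further gain to 82–83% comes from baseline adjustment.
- **The cut-off and the handling of ties may be in a fuller plan.** This stands in part. The article does not say that unchanged patients will be dropped, nor that the cut is at zero. It does commit to the switch and to two classes, so this is a stated method and not an omitted detail.
- **A proportion improved may be the intended estimand**, since the sample-size wording allows it. That would be a reason to fix it in advance, not to let a normality test select it.

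A reader might also infer bias or an inflated type I error. None of the calculations shows either.

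**Conclusion.** The point holds as a badly fixed method. Without any numerical assumption, the text lets a preliminary test choose the effect measure for every outcome, names two classes that leave out unchanged patients, and uses a test that cannot carry the adjustment in section 3.12. The size of the power loss does rest on assumptions. Under those of step 3, power falls from about 77–78% (t-test on change) or 74–75% (Mann-Whitney) to 38–49%. The loss is larger when more of the comparator arm improves, and absent for some right-skewed change. The exposure is clear for mRs and mAS. For TUG and TSMB it depends on the K-S version and the shape of the data.

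**What to change.** Delete the K-S gate and the improved/worsened chi-squared comparison. Pre-specify one primary analysis per outcome:

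- **TUG:** ANCOVA on log time with baseline log TUG as covariate. Add a rank-based sensitivity analysis that gives patients unable to complete the test the worst rank.
- **TSMB, BI, HADS, Euroqol:** ANCOVA on the baseline score, with a rank-based sensitivity analysis.
- **mRs, mAS, NIHSS:** proportional-odds model adjusted for baseline.

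These models can also carry the covariates of section 3.12. Report the proportion improved descriptively only, with unchanged patients shown as their own category. Section 5 says recruitment was ongoing at submission, so the change should be dated and made before outcomes are compared by group. It costs analysis wording only, with no new data or patients.
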